## Abstract

**Background:**

Vascular calcification is a common complication associated with chronic kidney disease and the major cause of cardiovascular disease in patients with end-stage renal disease. The vascular calcification risk burden is still unknown in China. This study aims to investigate the prevalence of vascular calcification and assess the predictive value of vascular calcification in patients with stage 5 chronic kidney disease on dialysis in China.

**Methods/Design:**

This is a national, multicenter, non-interventional, prospective cohort study planning to recruit 1520 patients with end-stage renal disease receiving hemodialysis or peritoneal dialysis for at least 6 months in 24 dialysis centers in China. All the patients provided written informed consents before participating in this study. It will include a baseline visit and 24 months follow-up period with 4 other visits at 6-month intervals. Vascular calcification images will be obtained to determine the prevalence of vascular calcification, coronary artery calcification, abdominal aortic calcification and cardiac valve calcification. Association between vascular calcification and all-cause and cardiovascular disease mortality and non-fatal cardiovascular events will be assessed. Disease management, as assessed by serum level of calcium, phosphorus and intact parathyroid hormone and its impact on vascular calcification, will also be surveyed.

**Discussion:**

The new results gained from this study will supplement limited current available data and provide better clinical decisions in Chinese patients with chronic kidney disease on dialysis.

## Background

Chronic kidney disease (CKD) is a critical health problem. It is estimated that there were nearly 120 million patients with CKD in China with an overall prevalence of 10.8 % [1]. It is similar to that in the United States (13.1 %) and Norway (10.2 %) but the awareness of CKD (10.04 %) is still relatively low in China [2–4]. The number of patients with end-stage renal disease (ESRD) is estimated to be 2 million in China, but less than 20 % of patients are undergoing dialysis [5].

Vascular calcification (VC) is a common complication associated with CKD and the major cause of cardiovascular disease (CVD) in patients with ESRD [6]. In contrast, patients without VC always have a better prognosis with limited progression of VC over a longer period of time [7]. The prevalence of VC increases as CKD progresses, from 40 % at stage 3 CKD to 80–99 % at stage 5 CKD on dialysis (CKD stage 5D) [8–12].

Mineral and bone disorder (MBD) is also a frequent complication of CKD associated with increased risk of VC, arterial dysfunction, morbidity and mortality [13]. A meta-analysis revealed that every 1.0 mg/dL of serum phosphorus was associated with 18 % increase of the risk of death in patients with CKD, indicating that hyperphosphatemia is an independent risk factor for mortality among those patients [14]. Hyperphosphatemia is increasingly considered the cause and a key factor inducing early and progressive VC in patients with CKD, implying that vigorous treatment of hyperphosphatemia with phosphate binders is essential to the prevention of VC [15, 16]. In addition, hyperphosphatemia is a key regulator involved in multiple mechanisms that induce and promote the progression of VC [15]. Therefore, prevention of MBD and lowering the circulating levels of phosphate and calcium have become major targets in the treatment of VC [17].

MBD management is not optimized for Chinese dialysis patients and hyperphosphatemia is an important issue needing greater awareness [18]. However, there is limited knowledge about the impact of VC on Chinese dialysis patients in current disease management and dialysis patterns. Additionally, the VC risk burden is still unknown in China, causing poorer prognosis and inadequate dialysis management. The China Dialysis Calcification Study (CDCS) is the first large, prospective, multicenter, observational cohort study to investigate the prevalence of VC using different non-invasive imaging techniques and to assess the predictive value of VC with associated risk factors for all-cause and CVD mortality in dialysis patients with CKD stage 5D in China.

## Methods/Design

### Study design

The CDCS is a national, multicenter, non-interventional, 24 month prospective cohort survey in CKD patients on dialysis. The study includes a baseline visit and 4 other visits at 6 month intervals. The estimated enrollment period is 10 months. It is planned to consecutively recruit 1520 patients with ESRD receiving stable hemodialysis (HD) or peritoneal dialysis (PD) for at least 6 months in 24 dialysis centers in China. Participating centers will be selected based on logistics constraints. Consecutive patients who fulfill the inclusion and exclusion criteria and are willing to participate will be included in the study (Table 1). Written informed consents were obtained from all patients before participation. Each site is expected to enroll approximately 30 patients. After that, enrollment will be competitive at all sites. This study will be able to mirror real life management of these patients. All statistical analyses will be performed using SAS 9.2 software (SAS Institute, Cary, NC, USA). All hypothesis tests will use two-sided tests with a significance level of 0.05.

**Table 1 Tab1:** Inclusion and exclusion criteria of the CDCS

Inclusion criteria	Exclusion criteria
Male or female patients ≥18 years old	Patients’ life expectancy <6 months
Patients with ESRD receiving stable HD or PD for at least 6 months	Patients with acute kidney injury, active inflammatory diseases, parathyroidectomy or evident malignancies
Patient or legally accepted representative willing to sign Data Release Consent Form.	Patients with conditions making arterial calcification measurements technically impossible or unreliable, such as cardiac arrhythmias, amputations or severe peripheral vascular lesions
	Concomitant diseases that affect calcium status and soft tissue calcifications (sarcoidosis, multiple myeloma, HIV, amyloidosis)
	Pregnant or lactating women or women planning to become pregnant in the 6 months following entry into the study

*ESRD* End-stage renal disease, *HD* Hemodialysis, *PD* Peritoneal dialysis, *HIV* Human immunodeficiency virus

CKD is defined as abnormalities of kidney structure or function, present for >3 months, with implications for health, according to Kidney Disease: Improving Global Outcomes (KDIGO) 2012 Clinical Practice Guideline for the Evaluation and Management of CKD (Table 2) [19].

**Table 2 Tab2:** Criteria for CKD (either of the following present for >3 months)

	Criteria
Markers of kidney damage (one or more)	Albuminuria (AER ≧30 mg/24 h; ACR ≧30 mg/g)
	Urine sediment abnormalities
	Electrolyte and other abnormalities due to tubular disorders
	Abnormalities detected by histology
	Structural abnormalities detected by imaging
	History of kidney transplantation
Decreased GFR	GFR <60 ml/min/1.73 m^2^ (GFR categories G3a–G5)

*GFR* Glomerular filtration rate, *AER* Albumin excretion rate, *ACR* Albumin-creatinine ratio

### Objectives

The primary objective for the CDCS is to determine the prevalence of VC in Chinese patients with CKD on HD or PD. The secondary objectives are:To test the hypothesis that a greater severity of baseline VC is associated with a higher risk for all-cause and CVD mortality, and non-fatal CV events in Chinese patients with CKD on HD or PD.To investigate the association between all-cause and CVD mortality, and non-fatal CV events and disease management (using serum levels of calcium, phosphorus and intact parathyroid hormone (iPTH), fibroblast growth factor 23 (FGF23) and related medications) in Chinese patients with CKD on HD or PD.To investigate the impact of current disease management on VC.To evaluate the control rate of patients achieving target goal of serum phosphorus, calcium and iPTH.To validate the cardiovascular calcification index (CCI) in Chinese patients with CKD on HD or PD.

### Data collection

Visit 1 is at baseline/study entry and the follow-up includes 4 visits at 6 ± 1 month, 12 ± 1 month, 18 ± 1 months and 24 ± 1 month, respectively. The flow chart of detailed data and sample collection can be found in Table 3. At baseline, eligible patients will be evaluated for demographic information, smoking, alcohol drinking status, biochemical data, dialysis variables, concomitant medications, and personal and family disease history. Physical measurements including weight, height, body mass index (BMI) and vital signs (blood pressure and heart rate) will be obtained. Older age (male >55 years, female >65 years), arterial hypertension, family history (mother, father, brother, sister, children) of premature cardiovascular disease (≤55 years male, ≤65 years female), smoking, impaired glucose tolerance and/or impaired fasting glucose, dyslipidemia, and obesity are considered potent cardiovascular risk factors. The baseline biochemical data will be obtained using local routine laboratory methods performed within a week at the start of the study. If laboratory tests of serum 25-hydroxyvitamin D (25-OH Vit D) and FGF23 cannot be conducted in some centers, blood samples for testing 25-OH Vit D and FGF23 will be sent by the site study staff to those centers that can perform the assay. Blood sample collection will be performed according to the laboratory manual. Results from routine samples defined as samples taken within a week at the visit. Serum phosphorus, total calcium and iPTH will be tested at each visit. Target level of serum phosphorus, total calcium and iPTH in CKD stage 5 are defined according to Kidney Disease Outcomes Quality Initiative (K/DOQI) and KDIGO guidelines, respectively (Table 4) [20, 21]. Total serum calcium is adjusted if serum albumin is <4g/dL to better reflect the free calcium, using the formula proposed by the US Bone Metabolism Association: corrected total calcium (mg/dL) = total calcium (mg/dL) + 0.8 × [4.0 − serum albumin (g/dL)]. Date, time, primary reason and characteristics of death with autopsy results if applicable and any supportive documents that relate to fatal and nonfatal CV events are defined as clinical outcomes, and will be collected during the follow-up.

**Table 3 Tab3:** Study flow chart of the CDCS

Procedures	Visit time (month)				
	Baseline	6 ± 1	12 ± 1	18 ± 1	24 ± 1
Data release consent form	●				
Demography data	●				
Inclusion/exclusion criteria	●				
Physical measurements (vital signs)	●				
Smoking and alcohol drink status	●				
Cardiovascular risk factors	●				
Disease history	●				
Concomitant medications	●	●	●	●	●
Hemoglobin, hematocrit	●				
Serum total calcium, phosphorus, iPTH	●	●	●	●	●
25-OH Vit D, FGF23	●		●		●
Glucose, HDL-C, LDL-C, TC and TG	●				
hs-CRP	●				
Serum albumin, ferritin, alkaline phosphatase	●				
Urea, uric acid, creatinine	●				
ABI	●				
Kt/V, dialysate calcium concentration	●				
Dialysis vintage, dialysis frequency and modality, membrane type	●				
EBCT or MDCT scan	●				●
Plain lateral lumbar radiograph	●				●
Echocardiography, LVMI/LVH	●				●
Clinical outcomes		●	●	●	●

*iPTH* Intact parathyroid hormone, *25-OH Vit D* serum 25-hydroxyvitamin D, *FGF23* Fibroblast growth factor 23, *HDL-C* High density lipoprotein-cholesterol, *LDL-C* Low density lipoprotein-cholesterol, *TC* Total Cholesterol, *TG* Triglyceride, *hs-CRP* High-sensitivity C-reactive protein, *ABI* Ankle-brachial index, *EBCT* Electron beam computed tomography, *MDCT* Multi-detector computed tomography, *LVMI* Left ventricular mass index, *LVH* Left ventricular hypertrophy

**Table 4 Tab4:** Target level of serum phosphorus, calcium and iPTH in CKD stage 5

Biochemical parameters	K/DOQI	KDIGO
Serum phosphorus	3.5–5.5 mg/dL (1.13–1.78 mmol/L)	Toward Normal [2.5–4.5 mg/dL (0.81–1.45 mmol/L)]
Corrected total calcium	8.4–9.5 mg/dL (2.10–2.38 mmol/L)	Maintain Normal [Healthy: 8.5–10.5 mg/dL (2.13–2.63 mmol/L)]
Serum iPTH	150–300 pg/mL (16.5–33.0 pmmol/L)	2–9 times the upper normal limit (65 pg/mL, 6.9 pmmol/L)

*K/DOQI* Kidney Disease Outcomes Quality Initiative, *KDGIO* Kidney Disease: Improving Global Outcomes, *iPTH* Intact parathyroid hormone

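### The calcium target is set on albumin-corrected calcium, but albumin is scheduled only at baseline, so corrected calcium cannot be computed as defined at the four follow-up visits

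*Protocol article*

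**What the plan says.** All places are in the protocol article.

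- **Objectives.** One secondary objective is "To evaluate the control rate of patients achieving target goal of serum phosphorus, calcium and iPTH". It names no visit.
- **Data collection, text.** "Serum phosphorus, total calcium and iPTH will be tested at each visit". On the correction: "Total serum calcium is adjusted if serum albumin is <4g/dL to better reflect the free calcium". The formula adds 0.8 mg/dL for each 1 g/dL by which albumin falls below 4.0 g/dL. Where the text introduces the targets it speaks of total calcium and points to Table 4.
- **Table 3.** The row "Serum total calcium, phosphorus, iPTH" is marked at baseline and at months 6, 12, 18 and 24. The row "Serum albumin, ferritin, alkaline phosphatase" has one mark, at baseline.
- **Table 4.** The calcium row is labelled "Corrected total calcium". The range is 8.4–9.5 mg/dL under K/DOQI and 8.5–10.5 mg/dL under KDIGO, with no restriction to a visit.
- **Secondary analysis.** Serum calcium is one of the disease-management variables in the Cox models for mortality and cardiovascular events, in the baseline logistic and linear models, and in the coronary calcification progression models.

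**The concern.** The rule needs albumin twice: to decide whether the correction applies (below 4 g/dL), and to compute it. Without a current albumin, even the patients who need no correction cannot be identified. At months 6 to 24 the scheduled data supply calcium but not albumin, and the article gives no rule for those visits. An analyst would have to compare uncorrected calcium with a corrected target, or reuse the baseline albumin.

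At stake are the calcium part of the control-rate objective after baseline, and calcium as an exposure wherever a model uses follow-up values. A later analysis plan can choose a workaround, but it cannot recover albumin that was never recorded.

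**Working it through.** The article states no figure that depends on this point, so there is nothing to reproduce. The check has three steps.

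**1. Schedule against formula**

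| Visit | Total calcium | Albumin | Corrected calcium computable as defined |
|---|---|---|---|
| Baseline | yes | yes | yes |
| Months 6, 12, 18, 24 | yes | no | no |

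That is one visit of five. The single albumin mark is not a sign of a broken table: the vitamin D and FGF23 row keeps its three marks at baseline, 12 and 24 months.

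**2. Size of the correction, from the article's formula**

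Correction = 0.8 × (4.0 − albumin). The K/DOQI window is 9.5 − 8.4 = 1.1 mg/dL wide; the KDIGO window is 10.5 − 8.5 = 2.0 mg/dL wide. The albumin values are illustrative.

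| Albumin, g/dL | Correction, mg/dL | Share of K/DOQI window | Share of KDIGO window |
|---|---|---|---|
| 3.8 | 0.16 | 15 % | 8 % |
| 3.5 | 0.40 | 36 % | 20 % |
| 3.0 | 0.80 | 73 % | 40 % |

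Carrying baseline albumin forward gives an error of 0.8 × the change in albumin (below 4 g/dL): 0.16 mg/dL for a change of 0.2 g/dL, and 0.40 mg/dL for 0.5 g/dL.

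**3. Effect on classification and on the control rate**

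None of these inputs is in the article; all are assumptions. Corrected calcium is normal with mean 9.2 and SD 0.8 mg/dL. Albumin is normal with mean 3.6, 3.8 or 4.0 and SD 0.4 g/dL, independent of corrected calcium. The correlation between baseline and follow-up albumin is 0.3 to 0.7. In the simulation, total calcium = corrected calcium − 0.8 × max(0, 4.0 − albumin).

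The true control rates follow directly:

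- K/DOQI: Φ((9.5 − 9.2)/0.8) − Φ((8.4 − 9.2)/0.8) = Φ(0.375) − Φ(−1) = 48.8 %.
- KDIGO: Φ((10.5 − 9.2)/0.8) − Φ((8.5 − 9.2)/0.8) = Φ(1.625) − Φ(−0.875) = 75.7 %.

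Patient-visits on the wrong side of the target:

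| Mean albumin | K/DOQI, uncorrected | K/DOQI, carried forward | KDIGO, uncorrected | KDIGO, carried forward |
|---|---|---|---|---|
| 3.6 | 27 % | 13–19 % | 17 % | 8–12 % |
| 3.8 | 17 % | 10–16 % | 11 % | 7–10 % |
| 4.0 | 10 % | 8–11 % | 6 % | 5–7 % |

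Control rate that would be reported:

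| Mean albumin | K/DOQI (true 48.8 %), uncorrected | K/DOQI, carried forward | KDIGO (true 75.7 %), uncorrected | KDIGO, carried forward |
|---|---|---|---|---|
| 3.6 | 48.2 % | 45.8–47.4 % | 63.8 % | 72.4–74.2 % |
| 3.8 | 49.0 % | 46.5–47.7 % | 68.4 % | 73.2–74.5 % |
| 4.0 | 49.2 % | 47.3–48.0 % | 71.7 % | 74.1–74.9 % |

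Uncorrected, the K/DOQI rate hardly moves because patients switch in both directions. That depends on the assumed mean. As a second illustration, take total calcium normal with SD 0.7 mg/dL and every patient at albumin 3.5 g/dL (correction 0.40). With mean total calcium 9.4 mg/dL, the K/DOQI rate is 31.1 % corrected and 48.0 % uncorrected. With mean 8.6 it is 56.7 % corrected and 51.3 % uncorrected. Both the direction and the size of the error change with the mean.

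**The case against.** - **No sentence says that calcium control is assessed at every visit.** This stands. The article says that calcium is tested at each visit and leaves the visit for the control rate open. A baseline control rate is fully computable. Use at follow-up is a reasonable inference from a target with no visit restriction, but it remains an inference.
- **The effect on the models is conditional.** This stands. The logistic and linear models are explicitly at baseline, where albumin is collected. The Cox models are not said to use time-varying calcium, and the progression models do not say which visit's calcium they use. If all use baseline calcium, none is affected.
- **Counts of misclassified visits overstate the harm to a rate.** This stands in part. Under the main assumptions the K/DOQI switches nearly cancel, but the KDIGO rate still moves by 4 to 12 points if calcium is left uncorrected, and the K/DOQI cancellation fails at other means.
- **A condensed article may leave the correction rule to fuller documents, and sites may hold routine albumin results.** This mitigates the point but does not remove it. The article allows routine results within a week of the visit, yet its schedule does not list albumin after baseline. A rule written elsewhere does not supply the values.

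A reader might infer that four of the five calcium measurements will be misclassified. The documents do not support that: four visits lack a same-visit albumin, and on the assumed values only a minority of patient-visits change class.

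**Conclusion.** The inconsistency is real and can be seen in the article alone: the target is defined on a variable that the schedule lets one compute at one visit of five. The other four visits are exposed to misclassification if follow-up calcium is used.

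The size rests wholly on assumed distributions. On those used here, about 10–27 % (K/DOQI) or 6–17 % (KDIGO) of patient-visits change class if uncorrected, and about 8–19 % or 5–12 % with baseline albumin carried forward. The control rate shifts by about 1 point or less (K/DOQI) or 4–12 points (KDIGO) if uncorrected, and by about 1–3 points if carried forward.

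It might be inferred that this undermines the study's main results. It does not: the primary prevalence objective, the sample size and baseline corrected calcium do not depend on follow-up albumin. The point should be fixed, but it is not critical.

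**What to change.** 1. Add serum albumin at months 6, 12, 18 and 24 in Table 3, from the sample already drawn for calcium or from the routine result within the one-week window that the article already allows. The cost is one routine analyte and one case report form field per visit. The Trial status section reports that recruitment was still open at submission, so for visits still ahead this can be done before the values are lost.
2. Where no same-visit albumin exists, report corrected calcium by a prespecified rule with a sensitivity analysis. Carrying baseline albumin forward is one candidate. On the assumed values it misclassifies fewer patient-visits than no correction at mean albumin 3.6 and 3.8 g/dL, but not always at 4.0. Setting every such value to missing would discard measured calcium and may be selective.
3. If albumin is not added, restrict the corrected-calcium control rate to baseline and label follow-up calcium as uncorrected.
4. State which visits the control rate and the calcium exposure use, and align the total calcium wording in the Data collection text with the corrected calcium of Table 4. Items 2 to 4 cost only wording and, for the sensitivity analysis, a little programming.

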### Secondary analysis

The key secondary analysis will be a comparison of survival (based on all-cause mortality) between patients with and without VC based upon the log-rank test performed at a significance level of 0.05. Hazard ratios and 95 % CIs will be calculated by a Cox proportional hazard regression model. In addition, the multivariable Cox proportional hazard regression model will be performed, using the stepwise method (*p* <0.05 as the inclusion criteria and *p* <0.10 as the exclusion criteria), considering with or without VC as the independent variable and the baseline variables with *p* <0.25 in univariate analysis as covariates, and hazard ratios and 95 % CIs for each factor will be presented. The same analyses will also be done for survival (based on CVD mortality) and non-fatal CV event free survival. For each of the above endpoints, the separate comparisons of patients with CAC, with AAC, with cardiac valve calcification to patients without VC will be made at a significance level of 0.05.

Association between disease management (including serum level of calcium, phosphorus and iPTH, and medications), 25-OH Vit D, FGF23, and all-cause/CVD mortality, non-fatal CV events will be identified with Cox proportional hazard regression model, considering disease management as the independent variables. Associations will be tested using the Wald test and described through the hazard ratios and 95 % CIs.

Association between disease management, 25-OH Vit D, FGF23, ankle-brachial index (ABI), and LVMI/LVH and the occurrence of CAC, AAC and cardiac valve calcification at baseline will be identified with the logistic regression model. The univariate logistic regression model will be performed separately, considering disease management, ABI, and LVMI/LVH as independent variables. Associations will be tested using the Wald test and described through the odds ratios and 95 % CIs.

Association between disease management, 25-OH Vit D, FGF23, ABI, and LVMI/LVH and severities (scores) of CAC, AAC and cardiac valve calcification at baseline will be identified with the linear regression model, considering disease management, ABI, and LVMI/LVH as independent variables.

Association between CAC progression and disease management, 25-OH Vit D, FGF23, ABI, as well as LVMI/LVH will be evaluated by ANCOVA as continuous variables and evaluated by ordinal multinomial logistic regression as categorical variables.

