## Discussion

VC is a major contributor to CVD, which is a significant cause of mortality in ESRD. However, the burden and management of VC in Chinese patients with CKD on dialysis are still unknown. Given that clinical trials are considered the best way to provide evidence and related knowledge for guidance, it is necessary to design a high quality national observational study that is capable of addressing these issues.

The CDCS is a uniquely-designed observational cohort study seeking to collect detailed clinical, biochemical and laboratory data to inform the prevalence and impact of management of VC in Chinese patients with CKD on dialysis, and test the hypothesis that baseline VC is a predictor for all-cause/CVD mortality and non-fatal CV events. This study aimed to recruit well-characterized patients in order to avoid incidence-prevalence bias, and the sample size will be large enough to achieve multiple study objectives with adequate variability [25].

This study may be limited by the nature of the design as an observational study, in comparison with randomized controlled trials which can commonly provide stronger evidence in the efficacy of therapies. Since the proportion of patients receiving HD or PD cannot be predefined, the strength of comparing the outcome between the two groups may be weakened. In addition, collection of some prognostic factors (e.g., brain natriuretic peptide and troponin) for CVD was not included in the study design as these tests will not be applicable for every enrolled patient in the real-world clinical practice setting.

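### The pooled HD and PD covariate selection in the Secondary analysis does not hold dialysis modality fixed, so modality-specific covariates are screened without adjustment for it

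*Protocol article*

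**What the plan says.** The cohort combines both modalities. Table 1 (Study design) admits "Patients with ESRD receiving stable HD or PD for at least 6 months".

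Table 3 (Data collection) lists, at baseline and with no HD-only or PD-only mark, "Kt/V, dialysate calcium concentration" and "Dialysis vintage, dialysis frequency and modality, membrane type". Modality is thus recorded for every patient.

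The Secondary analysis section fixes how the multivariable Cox model is built. Presence of vascular calcification (VC) is the exposure, and the covariates are "the baseline variables with *p* <0.25 in univariate analysis as covariates". Selection is stepwise, with entry at 0.05 and removal at 0.10, and "hazard ratios and 95 % CIs for each factor will be presented". The same procedure is repeated for cardiovascular mortality and for survival free of non-fatal cardiovascular events. No stratum, forced term or separate covariate list for modality is stated.

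The Discussion recognises that the HD/PD mix is not under control ("Since the proportion of patients receiving HD or PD cannot be predefined"), but draws a consequence only for comparing the two groups, not for the covariate model.

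**The concern.** Some Table 3 items do not mean the same thing in the two modalities. Kt/V is conventionally expressed per session in HD and per week in PD. Frequency counts sessions in one and exchanges in the other. Membrane type describes HD equipment. The article states none of this; it is general subject knowledge.

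If such items go through a univariate screen with HD and PD pooled, two things can happen. The pooled coefficient partly measures which modality the patient is on. And a real effect within each modality can be diluted or cancelled by the HD-PD difference, so that the variable fails the 0.25 screen and is never considered again, even if it would have been significant once modality was in the model. At stake are the reported covariate hazard ratios and the adjustment set behind the adjusted VC hazard ratio.

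**Working it through.** **1. The plan's own figure.** From Determination of sample size: 2-year survival 0.79 and 0.86, 1064 and 456 patients, 20 % lost. The hazard ratio θ is ln(0.86)/ln(0.79) = 0.6398, as stated. Freedman's formula with k = 456/1064 = 0.4286:

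events = (1.960 + 0.842)² (1 + kθ)² / [k(1 − θ)²] = 229.2

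The event rate is 0.7 × 0.21 + 0.3 × 0.14 = 0.189, so 229.2/0.189 = 1213 evaluable and 1213/0.8 = 1516, against 1520 planned. With 1520 patients the expected deaths are 1520 × 0.189 × 0.8 = 229.8, and power is 80.1 %. The design reproduces. This is the log-rank test, which uses no covariates. The 229.8 deaths are used below.

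**2. What a pooled Kt/V coefficient estimates.** All inputs are assumptions, because the article gives none: HD mean 1.35, SD 0.25; PD mean 1.85, SD 0.40 (difference Δ = 0.50); PD share p of 10 to 30 %; hazard ratio h per within-modality SD of Kt/V; PD:HD hazard ratio m. To a linear approximation:

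V = (1 − p)·0.25² + p·0.40² + p(1 − p)·Δ²

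pooled log hazard ratio per SD = {[(1 − p)·0.25 + p·0.40]·ln h + p(1 − p)·Δ·ln m} / √V

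Example, p = 0.20, h = 1, m = 1.6: V = 0.050 + 0.032 + 0.040 = 0.122, √V = 0.349; 0.16 × 0.50 × 0.470 / 0.349 = 0.108; hazard ratio 1.11.

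| PD share | √V | h = 1, m = 1.6 | h = 0.80, m = 1.6 | h = 0.80, m = 1.25 |
|---|---|---|---|---|
| 10 % | 0.308 | 1.07 | 0.88 | 0.85 |
| 20 % | 0.349 | 1.11 | 0.93 | 0.88 |
| 30 % | 0.380 | 1.14 | 0.96 | 0.89 |

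Simulated Cox models gave 1.06 to 1.15 and 0.88 to 0.96 for the first two scenarios. On the per-unit scale, a separate simulation (PD mean 1.9, hazard ratio 0.82 per within-modality SD, m from 0.8 to 1.25) had true values of 0.449 in HD and 0.607 in PD. The pooled values ran from 0.51 to 0.79, so they can fall outside both.

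**3. Passing the 0.25 screen.** The threshold is |z| > 1.15, and the expected |z| is about |log hazard ratio per SD| × √229.8 = |log hazard ratio| × 15.16.

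- Screened within modality, h = 0.80: 0.223 × 15.16 = 3.38, so the chance of failing is Φ(1.15 − 3.38), about 1 %.
- Pooled, m = 1.25: z = 2.41, 1.94 and 1.70 at 10, 20 and 30 % PD; chance of failing about 10, 21 and 29 %.
- Pooled, m = 1.6: z = 1.87, 1.08 and 0.65; chance of failing about 24, 52 and 66 %.

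**4. The full selection rule.** Modality is itself a candidate, so the pooled coefficient is not necessarily what would be reported. In simulations with Kt/V and modality as the candidates:

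- with no Kt/V effect and m = 1.6, Kt/V stays in without modality in only about 6 to 9 % of runs;
- with h = 0.80 and m = 1.25, neither variable is selected in about 19 to 35 % of runs, although both have an effect.

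**The case against.** The strongest objection is that modality can enter the model by itself. Where the HD-PD difference is large enough to distort Kt/V, it is usually large enough for modality to be selected, and the 6 to 9 % in step 4 bears this out. This stands against any claim that a spurious Kt/V hazard ratio is the likely result. It does not answer the loss of a real effect at the screen, which happens before modality is in any model. Nor does modality as a covariate repair a single slope fitted across two scales.

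A second objection is that the section does not name Kt/V, frequency or membrane type, and that recording conventions belong to the case report form or to an analysis plan not shown. That is fair for coding. The selection rule, however, is fixed in the article and applies to baseline variables without restriction. Nor are these covariates the subject of any stated objective, and no bias in the VC hazard ratio itself has been calculated.

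A reader might go further and infer three things that the document does not support.

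- **The planned 80 % power falls to about 76, 71 or 65 %** if 10, 20 or 30 % of patients are on PD and drop out. The arithmetic is right, but that power belongs to the log-rank test, which loses nobody through a covariate.
- **Membrane type removes every PD patient from the adjusted model.** That needs membrane type to pass the screen, to be blank for PD and the fit to be complete-case. The article fixes neither the coding nor the handling of missing values, and a not-applicable level would keep all patients.
- **The covariate hazard ratios are certain to be uninterpretable.** They can be confounded with modality and on mixed scales; how far depends on the mix and on what is selected.

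**Conclusion.** The point holds as a defect in how the multivariable Cox model is specified. One screen and one stepwise selection are applied to HD and PD together, and the one variable that should be held fixed, which is already collected, may be dropped.

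The size depends on assumed Kt/V distributions, a PD share of 10 to 30 % and the assumed PD:HD hazard ratio. In the scenarios where Kt/V is protective and PD carries the higher hazard, a hazard ratio of 0.80 is diluted to between 0.85 and 0.96. The chance of failing the screen rises from about 1 % to between 10 and 66 %. Other directions of effect would distort differently. That these items differ by modality is general knowledge, not a statement in the article.

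The prevalence analysis, the log-rank test, the unadjusted hazard ratio and the sample size are untouched. Loss of PD patients from the adjusted VC model is a conditional risk only.

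**What to change.** In the Secondary analysis section:

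- stratify the pooled Cox models, including the univariate screen, by dialysis modality, or force modality into each of them;
- if Kt/V and dialysis frequency are used as covariates, standardise them within modality or nest them within modality, since adjusting for modality alone leaves the difference in scale;
- keep membrane type out of the pooled candidate list and use it only in an HD analysis, so that no PD patient can be lost from the adjusted VC model.

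The cost is a change of analysis wording and a few extra model terms. No new data are needed, because Table 3 already collects modality and the covariates. The log-rank test and the sample size can stay as they are.
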